## Background, including rationale and any previous systematic reviews

Rates of obesity, as defined by a body mass index (BMI) greater than 30 kg/m^2^, are rising alarmingly in the UK and throughout the world. Around 27% of adults in Scotland are now obese and 32% of Scottish children have a weight outwith a healthy range for their age.^1^ Obesity rates in England^2^ and the USA^3^ are similar. The increase in average BMI during pregnancy over the past 20 years has been well documented.^4^ Rates of maternal obesity in women booking for antenatal care in the UK are now around 20%. There has also been a substantial increase in mean birth weight and in the incidence of being born large for gestational age over the past few decades.^5^ The secular rise in maternal weight at delivery appears to be the factor most strongly correlated with the increase in birth weight.^5^
^6^ Positive correlations have also been shown between birth weight and both maternal pregravid weight^7–9^ and weight gain in pregnancy,^10^ with odds of high birth weight some 2.4 times greater in morbidly obese compared with lean women.^11^

This increase in mean birth weight is of concern because it is linked to an increased likelihood of child and adult obesity. A systematic review showed a positive correlation between birth weight and obesity during adulthood.^12^ The association between high birth weight and later life obesity is also supported by two large epidemiological studies^13^
^14^ both of which found obesity to be a long-term correlate of high birth weight. A subsequent prospective study found that children who were large for gestational age at birth and exposed to an intrauterine environment of maternal obesity are also at increased risk of developing metabolic syndrome.^15^ Our own recent work suggests that offspring of obese pregnant women are at increased risk of premature death in adulthood.^16^ Thus, the increase in rates of maternal obesity are setting up a vicious cycle, leading to increased birth weight and increased rates of child and adult obesity, contributing to an epidemic of obesity which has become one of the most significant contributors to global ill health.

Women who are obese during pregnancy are also themselves at greater risk of a number of adverse outcomes, including gestational diabetes,^17^ pre-eclampsia^18^ and stillbirth.^19^

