Considerable evidence implicates insulin resistance or hyperglycaemia as the mechanism by which maternal obesity causes excessive neonatal birth weight. While modest insulin resistance is physiological in pregnancy and generates maternal glucose, free fatty acids and amino acids as substrates for fetal growth, obese pregnant women are more insulin resistant than their lean counterparts^6^ leading to a further amplification of nutrient availability with consequent excessive fetal growth. There is a strong correlation between insulin resistance in late gestation and both birth weight and fat-free mass at birth.^26^ The Hyperglycaemia and Adverse Pregnancy Outcomes (HAPO) trial^27^ confirms that there is a linear relationship between hyperglycaemia and birth weight, even at glucose levels not usually considered abnormal during pregnancy. The Australian Carbohydrate Intolerance Study in Pregnant Women (ACHOIS)^28^ confirms that treating hyperglycaemia can substantially reduce both the incidence of large for gestational age babies and other perinatal complications. Thus, metformin, by reducing insulin resistance, could have a major impact in reducing excess birth weight in obese pregnant women.

This study is timely because of emerging evidence about the safety and efficacy of metformin. It is a licensed first-line therapy for the treatment of type 2 diabetes and is endorsed by National Institute for Health and Care Excellence (NICE) as a treatment for gestational diabetes.^29^

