### Secondary objectives

To determine the pattern of association between insulin resistance and adverse pregnancy outcomes, including incidence of pregnancy-induced hypertension, pre-eclampsia, caesarean section, postpartum haemorrhage, maternal weight gain during pregnancy and incidence of the baby's admission to the neonatal unit.To determine the effect of metformin on maternal body composition.To determine the effect of metformin on neonatal body composition.To determine the effect of metformin on maternal inflammatory and metabolic variables (measured at 28 and 36 weeks’ gestation) and on neonatal inflammatory variables (measured in cord blood at birth).To confirm that metformin does not increase the rate of babies with a low birthweight centile.To determine the efficacy (as opposed to the effectiveness) of metformin when analysis is restricted to those with pharmacological circulating levels of drug.A series of nested substudies will also be performed with the following objectives:
To determine the effect of metformin on maternal cortisol levels in obese pregnant women.To determine the effect of metformin in hepatic and peripheral insulin sensitivity at 36 weeks’ gestation in obese pregnant women.To determine the effect of metformin on endothelium-dependent flow-mediated dilatation in obese pregnant women.To determine the effect of metformin on maternal subcutaneous and visceral adipose tissue deposition and hepatic and skeletal muscle ectopic fat deposition during pregnancy.To determine the effect of metformin on fetal liver volume and subcutaneous fat deposition.To determine the effect of metformin on myometrial contractility and myometrial glycogen storage in obese pregnant women.To determine the effect of metformin on placental glucocorticoid receptor and 11 βHSD 1 and 2 mRNA levels.

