## Randomisation

Eligible participants will be randomly assigned to active treatment with metformin or an identical looking placebo. This will be documented in the patient's paper case record and/or computer file to show the woman's participation in the trial.

Participants will be randomised via a web portal connected to a central randomisation facility based at the trial data centre, the Edinburgh Clinical Trials Unit, University of Edinburgh. Baseline eligibility data will be required before randomisation. Participants will be randomised in a 1:1 ratio to metformin or placebo. Randomisation will be stratified by treatment centre and BMI 30–39 vs >40 kg/m^2^.

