### Secondary outcomes

Maternal insulin resistance at 36 weeks’ gestation, which will be correlated with adverse pregnancy outcomes.Maternal anthropometry and body composition at 16 and 36 weeks’ gestation and 3 months postpartum.Baby anthropometry and body composition at birth and 3 months of age.Maternal inflammatory markers, lipid and fatty acid indices prior to starting treatment and again at 28 and 36 weeks’ gestation including CRP, IL-6, leptin, lipid profile, non-esterified fatty acids, polyunsaturated fatty acids and PAI1/PAI2 ratio.Neonatal CRP, glucose, insulin and other inflammatory and metabolic indices as previously described (measured in cord blood at birth).Incidence of low birthweight centile.Gas chromatography mass spectrometry measurement of metformin in maternal plasma to determine adherence.Secondary outcomes from nested substudies;
Maternal salivary cortisol levels at baseline, 28 and 36 weeks’ gestation.Hepatic and peripheral insulin sensitivity at 36 weeks’ gestation as measured by the hyperinsulinaemic euglycaemic clamp technique.Maternal brachial artery endothelium flow-mediated dilatation measured at 16 and 36 weeks’ gestation.Maternal subcutaneous and visceral adipose tissue deposition and hepatic and skeletal muscle ectopic fat deposition assessed using MRI and magnetic resonance spectroscopy.Fetal liver volume and fetal subcutaneous fat deposition assessed using MRI.In vivo measurements of myometrial contractility on myometrial biopsies obtained at the time of caesarean section.Placental glucocorticoid receptor and 11 βHSD 1 (β hydroxysteroid dehydrogenase 1) and 2 mRNA levels.

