### Type of analysis and statistical tests

The primary analysis will be by intention to treat. Mean birthweight centile will be compared between the two groups using a two-sample t test, but with the analysis stratified for the same factors as the randomisation. Correlations within the metformin and placebo groups will be used to determine associations between insulin resistance and adverse pregnancy outcomes.

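### Within-arm correlations are a poor fit for the insulin-resistance objective: five of its six named outcomes are yes/no, so the coefficients are not comparable across outcomes

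*Protocol article*

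**What the plan says.** The first item under Secondary objectives is "To determine the pattern of association between insulin resistance and adverse pregnancy outcomes, including incidence of pregnancy-induced hypertension, pre-eclampsia, caesarean section, postpartum haemorrhage", and the list ends with "maternal weight gain during pregnancy and incidence of the baby's admission to the neonatal unit". Of these six outcomes only maternal weight gain is continuous.

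Two places give the method. Secondary outcomes lists maternal insulin resistance at 36 weeks, "which will be correlated with adverse pregnancy outcomes". Type of analysis and statistical tests then states: "Correlations within the metformin and placebo groups will be used to determine associations between insulin resistance and adverse pregnancy outcomes". No other analysis is given for this objective. The article does not name the type of coefficient and does not mention covariates for it.

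On BMI, the Randomisation section states: "Randomisation will be stratified by treatment centre and BMI", with BMI in two bands. The analysis section applies the randomisation strata to the birthweight comparison and is silent on them for the correlations. Table 3 shows height and weight recorded at the consent visit, so baseline BMI is available.

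**The concern.** The objective asks how the association with insulin resistance varies over a set of outcomes. That needs an effect measure that keeps its meaning from one outcome to the next and from one arm to the other. A correlation with a yes/no variable does not. Two outcomes with the same odds ratio per unit of insulin resistance give different coefficients if one is rare and the other common. The same slope gives different coefficients in two arms if the spread of insulin resistance differs. A reader of the results could take a small coefficient for a rare complication as a weak link to insulin resistance when it partly reflects low incidence.

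There is also a question of confounding. Association within an arm is observational, and randomisation does not balance women with high against women with low insulin resistance. BMI is an obvious candidate confounder.

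**Working it through.** **The plan's own figures.** The article gives no figure for this objective. Its only sample-size figures concern birthweight and they reproduce: with d = 0.2/0.6 = 1/3, the two-sided 5% t test needs 142.2 per group for 80% power and 162.6 for 85%, which round up to the stated 143 and 163.

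**Inputs.** Five yes/no outcomes and one continuous outcome come from Secondary objectives. The number of women per correlation is about 200 (half of the roughly 400 under Design) or about 224 (half of the 449 randomised by January 2014, from the Abstract), before losses. The article gives no incidences, odds ratios, spread of insulin resistance or BMI correlations. All such values below are assumptions.

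**1. Dependence on incidence.** Let X be insulin resistance in SD units, standard normal, with logit P(Y=1|X) = a + bX and a chosen so that overall incidence is p. The point-biserial correlation is

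r = E[X·P(Y=1|X)] / √(p(1−p)).

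Numerical integration gives the following. The last column is the largest r possible, reached when the outcome is a pure threshold on X: φ(z)/√(p(1−p)), with z the normal quantile at 1−p.

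| Incidence | Odds ratio 1.5 | Odds ratio 2.0 | Odds ratio 2.0, SD × 0.7 | Largest possible r |
|---|---|---|---|---|
| 3% | 0.069 | 0.116 | 0.082 | 0.399 |
| 5% | 0.088 | 0.147 | 0.104 | 0.473 |
| 10% | 0.120 | 0.199 | 0.142 | 0.585 |
| 20% | 0.158 | 0.258 | 0.187 | 0.700 |
| 40% | 0.191 | 0.307 | 0.226 | 0.789 |

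At a constant odds ratio of 1.5, the coefficient at 40% incidence is 0.191/0.088 = 2.2 times that at 5%. At an odds ratio of 2.0, the ratio between 40% and 3% is 0.307/0.116 = 2.6.

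A biserial coefficient, which divides r by the last column, would narrow this without removing it: for odds ratio 1.5, 0.088/0.473 = 0.19 at 5% and 0.191/0.789 = 0.24 at 40%.

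**2. Dependence on spread.** With the odds ratio fixed at 2.0 per original unit and 20% incidence, r falls from 0.258 to 0.187 if an arm's SD is 0.7 times as large. For a continuous outcome such as weight gain, the same slope with the SD multiplied by k gives r′ = rk/√((rk)² + 1 − r²). With r = 0.30 and k = 0.8, this is 0.24/√(0.0576 + 0.91) = 0.244.

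**3. BMI.** Suppose insulin resistance has no effect at all and BMI alone drives the outcome, with odds ratio 1.3 to 2.0 per SD, a BMI–insulin resistance correlation of 0.2 to 0.6, and incidence 10% or 40%. The unadjusted correlation is then 0.02 to 0.18. The 5% critical value for a single correlation, tanh(1.96/√(n−3)), is 0.139 at n = 200 and 0.131 at n = 224. Of the 18 combinations, only the most extreme (0.184) exceeds it.

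The chance of a false association is approximately Φ(atanh(r)·√(n−3) − 1.96), plus a negligible lower tail. Take n = 200, BMI odds ratio 1.5 and correlation 0.4:
- 40% incidence: r = 0.076, 0.076 × 14.04 = 1.07, so about 19%.
- 10% incidence: r = 0.047, 0.047 × 14.04 = 0.66, so about 10%.

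Both exceed the nominal 5%, by amounts that depend wholly on the assumptions.

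**The case against.** The strongest defence is that this is one sentence in a condensed article. The type of coefficient and the covariates may be set in the full protocol or the statistical analysis plan, neither of which is shown. That stands for covariates. It does not answer the main point, because the article does name correlation as the method, and names it in two places.

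Second, a point-biserial correlation gives the same test as a two-sample t test of insulin resistance between women with and without the event. It remains a valid test of whether an unadjusted association exists. That stands.

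Third, incidence need not dominate. An odds ratio of 2.0 at 10% incidence gives r = 0.199, and 1.5 at 40% gives 0.191, so strength of association matters as well. No ranking of coefficients is announced. That stands against any claim that the coefficients would mainly order the outcomes by incidence. It also shows the difficulty: two quite different odds ratios yield the same coefficient.

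Fourth, the article expects metformin to improve insulin sensitivity, which is a change in level, and says nothing about spread. Nor does it announce a comparison of coefficients between arms. A drop from 0.30 to 0.244 would be within noise: (0.3095 − 0.2490)/√(2/197) = 0.6 standard errors at 200 per arm. The between-arm problem is therefore conditional.

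A reader might go further and infer that the analysis is unadjusted and that its results will reflect BMI. The text supports neither. It is silent on adjustment. Its background statements are "obese pregnant women are more insulin resistant than their lean counterparts" and "Women who are obese during pregnancy are also themselves at greater risk of a number of adverse outcomes". The first contrasts obese with lean women and the second concerns obese women as a group. Neither shows a gradient in BMI among women who all have a BMI of at least 30. False-association rates worked out for 400 women would not apply either, since each correlation uses one arm.

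**Conclusion.** The concern holds as a mismatch between a stated method and a stated objective. Correlation is fixed for a set of outcomes that are five-sixths yes/no. The coefficients are not comparable across those outcomes: roughly a twofold difference between 5% and 40% incidence at a constant odds ratio of 1.5, where both the odds ratio and the incidences are assumed. They are not comparable between arms either if metformin alters the spread of insulin resistance, which the article does not say. The method can detect an unadjusted association but cannot describe how associations compare.

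Confounding by BMI is a plausible reason to include it as a covariate. It is not a demonstrated error. The point concerns a secondary, explanatory objective and leaves the randomised primary comparison as it is.

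**What to change.** In Secondary outcomes and in Type of analysis and statistical tests, replace the correlations with logistic regression for the five yes/no outcomes and linear regression for maternal weight gain. Report odds ratios or slopes with 95% confidence intervals per one fixed unit of log insulin resistance, the same in both arms, for example the pooled or the placebo-arm SD. Using each arm's own SD would bring the dependence on spread back. Include baseline BMI as a prespecified covariate. If the arms are to be compared, fit one model with a treatment-by-insulin-resistance term instead of setting two coefficients side by side.

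This costs wording only; no new data are needed. The drawback is that rare outcomes will give wide intervals or need a penalised fit. Odds ratios also depend on which covariates are in the model, so the same covariate set should be used for every yes/no outcome.

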## Interim analysis and stopping rules

No formal interim analysis is planned (other than those requested by the Data Monitoring Committee (DMC)).

## Committee oversights

There is an independent Trial Steering Committee and an independent Data Monitoring Committee to oversee the safety of the participants in the trial.

## Discussion

Despite recognition that obesity represents a major public health problem, and that adult obesity may have its origins before birth, there is a lack of any effective intervention for obese pregnant women to improve pregnancy outcomes and reduce the future life risk of obesity for their offspring. In light of convincing evidence that the harmful effects of obesity during pregnancy are related to hyperglycaemia or insulin resistance, treatment during pregnancy with metformin is an exciting potential therapy. The Efficacy of Metformin in Pregnant Obese Women, a Randomised controlled (EMPOWaR) trial is designed to establish whether improving insulin sensitivity in pregnancy mitigates some of the adverse risk associated with obesity, with the primary aim of examining the effect on the birth weight of the baby, using birth weight as a surrogate marker of future life risk of obesity. A series of embedded mechanistic studies will help us to understand more about the mechanism of effect of metformin.

If our study finds metformin to be beneficial in reducing excess birth weight in obese pregnant women, it presents a potential future therapy where none currently exist. Clearly further large studies will be required to corroborate our findings. To our knowledge, there is currently only one other randomised double-masked placebo-controlled trial in progress which aims to recruit 850 women with a BMI >35 kg/m^2^ and is due to complete in September 2014 (Shehata, http://clinicaltrials.gov/show/NCT01273584).

As for any drug trial in pregnant women, safety is clearly a priority. Metformin has been used for decades in pregnant women with no evidence of any teratogenic effects. We do not expect any adverse effects from teratogenicity in our study population. There is no evidence from previous studies that metformin increases the incidence of babies with a low birthweight centile and we hope to confirm this with our data. Longer term follow-up studies of the offspring will be needed to assess the benefits or adverse effects in later life of antenatal exposure to metformin.

Finally, metformin is an inexpensive drug, costing under £5 per month. Obesity and the associated maternal and fetal complications are a huge financial burden on health services.^37^ If metformin were found to be effective, its use could contribute to significant financial savings for health services.
